### Study intervention

Prior to the start of the trial, HPN patients have been screened for *S. aureus* carriage with swabs of the nose, throat, rectum, exit-site catheter, and body regions on indication (e.g. stoma, wound, skin lesion). Subsequently, enrolled patients will visit the regular outpatient clinic appointments every 6 months, in accordance with current guidelines [10].

After randomization, patients will be allocated to one of the following two treatment strategies:*Search and destroy (SD) strategy* focuses on the quick and short, systemic antibiotic eradication of *S. aureus* (Fig. 4)*.* Patients will receive treatment with mupirocin nasal ointment, a chlorhexidine oropharyngeal rinse and body wash, and two systemic antibiotics for one week, according to the Dutch MRSA guideline [10]. Hygienic measures consist of wearing clean clothing every day and frequent change of towels and bed clothes during treatment. Combination therapy is indicated because of improved effectiveness and a decreased chance of developing resistance. After one cycle of treatment, a set of body swabs (nose, throat, rectum, exit-site catheter, and body regions on indication (e.g. stoma, wound, skin lesion) will be taken weekly for 3 weeks to confirm total eradication. In case of persistent *S. aureus* carriage, patients will be treated again. Patients will not receive more than three treatment cycles per round. A successful treatment is defined as three consecutive negative sets of surveillance cultures obtained at least 48 h after completion of treatment and distributed over a period of at least 14 days. Treatment failure is defined when a patient is still a *S. aureus* carrier after three treatment cycles. Relapse of *S. aureus* carriage will be subsequently monitored at the standard new swab rounds, every 3 months. In case of relapse, patients will be treated again as well.*Continuous suppression (CS) strategy* focuses on the continuous, topical eradication o*f S. aureus* (Fig. 5)*.* Whether or not patients are carriers during the year, they will receive mupirocin nasal ointment, an oropharyngeal chlorhexidine rinse, and body wash for extra-nasal body regions every month for 5 days. The same hygienic measures as in the SD strategy group will be applied. Standard swabs of the nose, throat, rectum, exit-site catheter, and other body regions on indication will be taken every 3 months to monitor full body eradication.

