### Outcome measures

*Primary outcome*
Proportion of patients in whom *S. aureus* is totally eradicated during a 1-year time period.Total eradication is defined as 100% of all swabs (nose, throat, rectum, exit-site catheter, and body regions on indication) being negative for *S. aureus* per measured time point.
*Secondary outcomes*
Secondary outcomes are listed in Table 1.

**Table 1 Tab1:** Secondary outcome measures

Secondary outcome measure	Data collection instrument or method
Incidence of *S. aureus* infections	(S)AE forms every 3 months
Overall incidence of infections	(S)AE forms every 3 months
Mortality	Data from electronic patient file
Long-term antimicrobial resistance	Culture results every 6 months and NGS
Number of catheter removals	Data from electronic patient file
Time to first catheter-related infection	(S)AE forms every 3 months and data from electronic patient file
Successful *S. aureus* eradication per body site	Culture results
Relapse rate of *S. aureus* carriage	Culture results and NGS
Transmission routes	Caregivers culture results and NGS
*S. aureus* transmission routes	NGS
Adverse events	(S)AE forms every 3 months
Predictors for infections and treatment failure or success	Binominal regression analysis
Patient compliance	Medication files, counting pills, trial-specific medication diary, modified Morisky Medication adherence questionnaire
Generic health related quality of life	EuroQol 5 dimension, 5 levels questionnaire (EQ5D-5 L)
Treatment satisfaction	TSQM vII questionnaire
Healthcare related costs	iMCQ questionnaire

*iMCQ* iMTA Medical Consumption Questionnaire, *NGS* next-generation sequencing, *(S)AE* (serious) adverse event, *TSQM* Treatment Satisfaction Questionnaire for Medication

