##### Secondary study parameter(s)

Continuous data such as patient characteristics (age, sex, venous access, CRBSIs) will be presented as means ± standard deviation and in case of skewed distributions as medians and range. Dichotomous outcomes will be summarized as percentages (N events/N total). Parameters will be compared between both groups by the Student’s *t*-test, Wilcoxon rank sum test, Chi2-test or Fischer exact test depending on the type of outcome and distribution. A two-tailed *p* value < 0.05 is considered statistically significant. No corrections for multiple tests are applied. Known predictors (such as socio-economic status, pet ownership, location of *S. aureus* carriage, *S. aureus* carriage by caregiver, and active skin disease) for infections and treatment failure/success will be analyzed using a logistic and/or linear regression model.

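### The relapse-rate comparison lets the two arms enter the risk set by different rules and at different times, so equal true relapse can show as a difference in either direction

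*Protocol article*

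**What the plan says.** Table 1 of the protocol article (Outcome measures) lists one relapse outcome for both arms: "Relapse rate of *S. aureus* carriage Culture results and NGS". It gives no time origin or denominator. Under Secondary study parameter(s), dichotomous outcomes are summarized as percentages, events over total, and "Parameters will be compared between both groups by the Student’s *t*-test, Wilcoxon rank sum test, Chi2-test or Fischer exact test", depending on outcome type and distribution.

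The Study intervention section sets different swab rules for the two arms.

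- **SD.** After a one-week cycle, swab sets "will be taken weekly for 3 weeks to confirm total eradication". Success has its own rule: "A successful treatment is defined as three consecutive negative sets of surveillance cultures obtained at least 48 h after completion of treatment", spread over at least 14 days. A positive result in this window is not relapse: "In case of persistent *S. aureus* carriage, patients will be treated again", up to three cycles per round. Only afterwards is relapse looked for: it "carriage will be subsequently monitored at the standard new swab rounds, every 3 months".
- **CS.** Standard swabs "will be taken every 3 months to monitor full body eradication". No confirmation series is scheduled, and neither success nor relapse is defined for this arm.

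The only eradication criterion that can apply to CS is the general one under Outcome measures: every swab negative at a measured time point, which one set can satisfy.

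**The concern.** Only a patient who has been declared free of carriage can relapse. The route to that state differs between the arms in two ways.

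1. **Time at risk.** An SD patient can be declared free after about four weeks and then faces four routine rounds. A CS patient, colonized at entry by the inclusion criteria, can first be negative at month 3 and faces at most three further rounds.
2. **Certainty of entry.** SD requires three negative sets, CS in effect one. A carrier missed at a single set is admitted to the CS risk group and later counted as a relapse.

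A simple test of one percentage against the other would mix these schedule effects with any real difference in durability. Long-term decolonization is the trial's aim, so readers will look at this outcome although it is secondary.

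**Working it through.** **The plan's own figures.** The article gives no expected relapse rate, so there is none to reproduce. Its sample size does reproduce with the unpooled two-sided formula: (1.960 + 0.842)² × (0.55×0.45 + 0.77×0.23) / 0.22² = 68.86, so 69 per arm. Relapse does not enter it.

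**Inputs from the article.** One-week SD cycle plus three weekly sets, so day 28 (0.92 months) at the earliest; routine rounds at months 3, 6, 9 and 12; culture sensitivity 95–97%; planning eradication rates 77% (SD) and 55% (CS).

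**Assumptions.** The same constant relapse hazard in both arms; 12-month relapse risk R from 10% to 50%; first relapse only; the quoted sensitivity holds for a whole set; the three SD sets err independently; 23% to 45% still carrying at confirmation (the complements of the planning rates).

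**Step 1: time at risk, perfect swabs.** SD is at risk for 12 − 0.92 = 11.08 months, CS for 12 − 3 = 9 months. The crude percentages are 1 − (1−R)^(11.08/12) and 1 − (1−R)^(9/12).

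| R | SD | CS | Excess in SD (points) |
|---|---|---|---|
| 10% | 9.3% | 7.6% | 1.7 |
| 20% | 18.6% | 15.4% | 3.2 |
| 30% | 28.1% | 23.5% | 4.6 |
| 50% | 47.3% | 40.5% | 6.7 |

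The ratio falls from 1.22 to 1.17 as R rises.

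**Step 2: repeat cycles.** Take a hazard of 5% to 20% per 3-month interval and assume 28 days per full cycle. The SD excess is 3.0 to 7.3 points if confirmed at day 28, 1.7 to 4.2 at day 56, and 0.3 to 0.9 at day 84. A CS patient first negative after month 3 has less time at risk, which works in the opposite direction.

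**Step 3: person-time instead of a percentage, perfect swabs.** At R = 20%, SD has 0.186 relapses over 10.28 months per patient and CS 0.154 over 8.52 months. Multiplied by 12, both give 0.217 per person-year. The schedule effect disappears.

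**Step 4: missed carriers.** With carrier prevalence p and sensitivity s, the falsely admitted fraction is p(1−s)/[p(1−s) + 1−p] after one set, and the same with (1−s)³ after three.

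- One set: from 0.0069/(0.0069 + 0.77) = 0.9% (s = 97%, p = 23%) to 0.0225/(0.0225 + 0.55) = 3.9% (s = 95%, p = 45%).
- Three sets: about 0.01% or less.

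Carrying these patients through the visits at R = 20%:

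- Crude percentage: SD 18.4–18.5%, CS 16.0–18.5%.
- Rate per person-year: SD 0.214–0.215, CS 0.227–0.266. CS is thus about 5% (0.2265/0.2155) to 24% (0.266/0.214) higher although the true hazard is the same.

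**Step 5: one rule in both arms.** If both arms enter on a negative month-3 set and p is equal, the results coincide: 15.4% and 0.217 in each with perfect swabs.

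**The case against.** The strongest reply is that the article does not say CS eradication is confirmed by a single set, nor that relapse will be tested as a crude percentage. A missing definition is something an article may leave to the full protocol or the analysis plan. This stands in part: single-set entry in CS is an inference. But the article itself fixes a three-set rule for one arm and schedules no other swabs in the other, and it names percentages and simple tests for dichotomous secondary outcomes. Those fixed features create the imbalance. A later plan can only work around it with the shared 3-monthly sets.

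A second reply is that a true rate removes the problem. Step 3 confirms this for perfect swabs; Step 4 shows that unequal entry then biases the rate in the other direction.

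A reader might also infer a spurious SD excess of 4.3 to 10.2 points, by setting four full quarters against three: 1 − (1−h)⁴ versus 1 − (1−h)³ for h from 5% to 20%. The article does not support that figure. SD confirmation cannot come before about day 28, so the first interval is short, and repeat cycles shorten it further.

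Finally, durability is mainly addressed by the primary outcome, which uses one definition and repeated measures in both arms. That is correct and limits the importance of this point.

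**Conclusion.** The point holds for the secondary relapse outcome only. As written, the arms differ in how and when patients enter the risk set and in how often carriers are let in by mistake. Under equal true hazards a crude percentage is higher in SD by about 2 to 7 points (assumed 12-month risk 10% to 50%, confirmation at day 28), and by less when cycles are repeated. Missed carriers raise the CS figure, enough in one scenario to cancel the crude difference (18.4% versus 18.5% at 95% sensitivity and 45% still carrying) and to put the CS person-time rate about 24% higher.

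It would be wrong to conclude that the comparison is biased against SD. The net direction depends on the metric and on the sensitivity of a full swab set, which is unknown: the quoted 95–97% is for enriched culture, and PCR is used as well. What can be said is that a difference in relapse rate, or the lack of one, could not be read as a difference in durability. The primary outcome and sample size stand.

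**What to change.** For the between-arm comparison, define relapse identically from the swabs both arms share: a positive 3-monthly set following a negative 3-monthly set. Report it per eligible 3-month interval or per person-time, not as a crude percentage of patients. Label it descriptive, because it conditions on eradication achieved after randomization. The SD three-set rule for treatment decisions stays unchanged.

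The cost is wording only; no extra swabs are needed. The downside is that SD relapses found at month 3 after three-set confirmation fall outside the common rule. They should be reported beside it, with the SD weekly sets described separately.

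The common rule reduces the distortion but does not remove it if more CS than SD patients still carry at entry. At 95% sensitivity, with 23% carrying in SD and 45% in CS, the rates under equal true hazard would be 0.233 and 0.266. That is a 14% gap (0.266/0.233), compared with 24% (0.266/0.214) under the present unequal entry. The report should state this limit.

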**Fig. 4 Fig4:**
[figure not shown]
Search and destroy group strategy. Flow chart of the search and destroy group treatment strategy

**Fig. 5 Fig5:**
[figure not shown]
Continuous suppression group strategy. Flow chart of the continuous suppression group treatment strategy

### Outcome measures

*Primary outcome*
Proportion of patients in whom *S. aureus* is totally eradicated during a 1-year time period.Total eradication is defined as 100% of all swabs (nose, throat, rectum, exit-site catheter, and body regions on indication) being negative for *S. aureus* per measured time point.
*Secondary outcomes*
Secondary outcomes are listed in Table 1.

**Table 1 Tab1:** Secondary outcome measures

Secondary outcome measure	Data collection instrument or method
Incidence of *S. aureus* infections	(S)AE forms every 3 months
Overall incidence of infections	(S)AE forms every 3 months
Mortality	Data from electronic patient file
Long-term antimicrobial resistance	Culture results every 6 months and NGS
Number of catheter removals	Data from electronic patient file
Time to first catheter-related infection	(S)AE forms every 3 months and data from electronic patient file
Successful *S. aureus* eradication per body site	Culture results
Relapse rate of *S. aureus* carriage	Culture results and NGS
Transmission routes	Caregivers culture results and NGS
*S. aureus* transmission routes	NGS
Adverse events	(S)AE forms every 3 months
Predictors for infections and treatment failure or success	Binominal regression analysis
Patient compliance	Medication files, counting pills, trial-specific medication diary, modified Morisky Medication adherence questionnaire
Generic health related quality of life	EuroQol 5 dimension, 5 levels questionnaire (EQ5D-5 L)
Treatment satisfaction	TSQM vII questionnaire
Healthcare related costs	iMCQ questionnaire

*iMCQ* iMTA Medical Consumption Questionnaire, *NGS* next-generation sequencing, *(S)AE* (serious) adverse event, *TSQM* Treatment Satisfaction Questionnaire for Medication

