**Methods/design:**

The CARRIER trial is a randomized, open-label, multicenter clinical trial in Dutch and Danish hospitals that treat patients on HPN. A total of 138 adult HPN patients carrying *S. aureus* will be randomly assigned to a search and destroy (SD) strategy, a quick and short, systemic antibiotic treatment, or a continuous suppression (CS) strategy, a repeated chronic topical antibiotic treatment. The primary outcome measure is the proportion of patients in whom *S. aureus* is totally eradicated during a 1-year period. Secondary outcomes are time to successful eradication, long-term antimicrobial resistance, adverse events, patient compliance, incidence of (*S. aureus*) infections, catheter removals, mortality rates, *S. aureus* transmission routes, quality of life, and health care costs.

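### The primary endpoint is not limited to the swab sets both arms share, and CS swabs have no stated interval from the monthly course, so the comparison can be biased

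*Protocol article*

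**What the plan says.** **Endpoint.** Outcome measures gives the primary outcome as "Proportion of patients in whom *S. aureus* is totally eradicated during a 1-year time period". A set counts as eradicated when every swab in it is negative: "Total eradication is defined as 100% of all swabs (nose, throat, rectum, exit-site catheter, and body regions on indication) being negative for" the organism. The rule applies to sets "being negative for *S. aureus* per measured time point". The time points are not listed.

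**Swabs common to both arms.** Study intervention and Follow-up give both arms sets at months 3, 6, 9 and 12.

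**Swabs in SD only.** Under Study intervention, sets after a treatment cycle "will be taken weekly for 3 weeks to confirm total eradication". Persistent carriage leads to another cycle, with at most three cycles per round. Treatment success in this arm means "three consecutive negative sets of surveillance cultures obtained at least 48 h after completion of treatment and distributed over a period of at least 14" (the unit is days).

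**CS.** The topical course is given for 5 days every month, whether or not the patient is a carrier. The standard swabs "will be taken every 3 months to monitor full body eradication". No interval between course and swab is given.

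**Model.** Primary study parameter(s) names a logistic mixed model for repeated dichotomous measurements. It does not say which measurements enter or whether there is a visit term.

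**The concern.** There are two separate problems.

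1. **Which sets count.** The SD weekly sets are measured time points, and the article says that they confirm total eradication, which is the term it defines as the primary endpoint. Read literally, the definition admits them, and CS has no counterpart. Their number depends on the outcome, since a patient who stays positive gets more of them, and they are taken shortly after systemic treatment. Pooled in the model they could favour SD; under a rule that every set must be negative they would penalise SD. The trial is open-label, so an open choice could be made with knowledge of the results.

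2. **When CS sets are taken.** Quarterly swabs fall on multiples of a monthly cycle. A set taken during or just after mupirocin and chlorhexidine may be negative because growth is suppressed at that moment. That could raise observed CS eradication and shrink the difference that the trial is powered to find. Restricting the endpoint to quarterly sets does not cure this.

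**Working it through.** **The plan's own figure.** Inputs from Sample size and power calculation: 77% (SD), 55% (CS), power 80%, α 5% (two-sided assumed), 1:1. With unpooled variance:

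n = (0.55×0.45 + 0.77×0.23) × (1.960 + 0.842)² / 0.22² = 0.4246 × 7.85 / 0.0484 = 68.9, so 69 per arm and 138 in total. The stated size reproduces.

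Power below uses the pooled variance under the null:

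z = [d − 1.96√(2p̄(1−p̄)/n)] / √[(p₁q₁ + p₂q₂)/n]

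At 55% against 77%, n = 69: z = (0.22 − 0.1581)/0.0784 = 0.79, so power is 78.5%. This is the reference value.

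**Number of sets in the year**

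| Arm | Quarterly | Weekly, per round | Total with one round |
|---|---|---|---|
| CS | 4 | 0 | 4 |
| SD | 4 | 3 per cycle × 1 to 3 cycles = 3 to 9 | 7 to 13 |

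**Effect of the extra SD sets.** The article gives no set-level rates, so every rate here except the planned 77% and 55% is an assumption.

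*(a) All sets pooled.* Suppose both arms are truly 65% negative on the quarterly sets.
- Three weekly sets at 80%: SD mean = (4×0.65 + 3×0.80)/7 = 71.4%. Apparent OR = (0.714/0.286)/(0.65/0.35) = 1.35.
- Six weekly sets at 90%: SD mean = (4×0.65 + 6×0.90)/10 = 80%. Apparent OR = 2.15.

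Simulating this null case (69 per arm, weekly sets 80–90% negative, up to three cycles, random-intercept SD 1–2, 300 trials per scenario) gives:

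| Random-intercept model, all sets included | OR | False-positive rate |
|---|---|---|
| No visit term | 1.60–2.19 | 34–91% |
| One term separating weekly from quarterly sets | 0.93–1.03 | 4–7% |

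The direction also depends on the weekly rate. Starting from a quarterly SD rate of 77%, three weekly sets at 50%, 77% or 95% negative move the SD mean to 65%, 77% or 85%.

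*(b) Every set must be negative.* If sets were independent, a true four-set SD rate of 77% implies 0.77^(1/4) = 0.937 per set. With 3, 6 or 9 extra sets, SD would read 0.937⁷ = 63%, 0.937¹⁰ = 52% or 0.937¹³ = 43%. Independence gives the upper bound. With perfectly correlated sets the effect is zero.

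**Timing of CS sets.** Assume swabs fall at random in a 30-day month.
- On treatment days: 5/30 = 17%.
- On treatment days or within 48 h after: (5 + 2)/30 = 23%.

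If the affected sets are 90% negative instead of 55%:
- 17% affected: CS = 0.55 + 0.167×0.35 = 60.8%; power against 77% is about 54%.
- 23% affected: CS = 0.55 + 0.233×0.35 = 63.2%; z = (0.1383 − 0.1528)/0.0771 = −0.19; power is about 43%.

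Without the 90% assumption: if observed CS eradication rose by 5, 10 or 15 points for any reason of timing, power would be 58%, 34% or 15%.

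**The case against.** The case on the other side is substantial.

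- **The weekly sets have their own role.** They guide re-treatment and define SD treatment success and failure, while the quarterly rounds are the standard swabs in both arms. The natural reading is that the quarterly sets carry the analysis. This stands to the extent that a reader might infer from the article that arm-specific sets decide the endpoint and that the comparison is therefore biased. No section says so. But none excludes them either, and the shared term leaves the literal reading open.
- **The 48 h rule.** A reader might infer that SD endpoint swabs are protected by the rule and CS swabs are not. The words "obtained at least 48 h after completion of treatment" belong to the definition of SD treatment success and are not stated for the quarterly sets of either arm. What remains is that CS, treated every month, has no stated gap.
- **Magnitude.** False-positive rates up to 91% need a model with no visit term and assumed rates. With such a term the inflation disappears. They are a worst case, not a forecast.
- **The CS illustration.** It treats the planned 55% as the rate away from treatment, whereas the article gives it as the strategy's rate over 1 year. Shares well above 23% would need swabs and courses to be aligned, which is not stated.
- **Time to eradication.** The abstract says "Secondary outcomes are time to successful eradication, long-term antimicrobial resistance", but Table 1 does not list time to eradication. The unequal swab schedule would affect it too, but it cannot carry a point about the primary comparison.
- **Condensed source.** Figs. 3–5 are not shown, and the full protocol or SAP may settle both questions. That limits certainty. Even so, the article does define the endpoint, and which measurements form it is part of that definition.

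**Conclusion.** The concern holds as a risk created by the endpoint wording, not as demonstrated bias.

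The definition does not confine the primary endpoint to the sets both arms share. If the SD weekly sets enter, ascertainment differs by arm. The bias could go either way and range from nothing to large, depending on set-level rates, the correlation between sets, and whether the model has a visit term; the article gives none of these.

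The missing gap between CS courses and swabs is a second weakness, and here the expected direction is towards CS. About 17% of CS sets would fall on treatment days and about 23% on or within 48 h of them, given random timing in a 30-day month. The fall in power from about 78% to about 43% also assumes 90% negativity in the affected sets and 55% in the rest, so it is an illustration.

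The sample size of 138 is not affected.

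**What to change.** 1. **Name the endpoint sets.** State that the primary endpoint and its mixed model use only the month 3, 6, 9 and 12 sets in both arms. Use the SD weekly sets for treatment decisions and for descriptive or secondary reporting.
2. **Use one swab-timing rule.** Apply the protocol's existing minimum of 48 h after treatment to every quarterly endpoint set in both arms. Do this by scheduling the swab, without altering treatment. Record the time from the last course to each swab.

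Do not require CS sets to be taken only just before the next cycle. That would sample the CS strategy only at its lowest point, with no SD equivalent, and could tilt the comparison towards SD.

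**Cost.** Two sentences in the protocol or SAP, a line in the swab instructions and one recorded date. The SD weekly sets no longer count towards the primary endpoint, and some swab dates shift by a few days. There are no new visits or swabs, and N stays 138.
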